#### Interaction With the Robot (T1)

The user, who has been deemed suitable and agreed to participate, starts the interaction with the robot assigned. In both cases, the researcher will suggest touching the robot’s head to initiate the interaction. From this point onwards, the researcher will not intervene in the interaction between the user and the robot, and the user will be free to interact with the robot and to stop the interaction at any time. When an explicit support request is made by the user, the researcher can intervene a maximum of 3 times, in line with good practice in experiments involving HRI analysis. At this point, the robot greets the user and asks how they can be helped, using the phrase “Good morning and welcome to INRCA. I’m (robot’s name) and I’m here to provide useful information to help you reach your desired destination within the hospital. Which department do you need to reach, or which exam do you need to take? Please, answer by saying only the name of the department or the exam as soon as my eyes turn blue.” At this point, the user responds, and the robot replies in one of two ways:

If it does not understand the request (or if the request is outside the robot’s knowledge), it invites the user to rephrase it and they return to the previous point; andIf it understands the request, it explains the path that the user should follow. In the case of Pepper, this path will also be shown on a display with photographic materials integrated with directional arrows.

After 1 successful interaction or 2 failed attempts, the robot asks the user if it has provided all the necessary information. If so, the robot says goodbye to the user as follows: “Thank you for participating. Have a nice day.” Otherwise, the interaction resumes from the point where the robot asks for the department to be reached or the test to be performed.

The researcher suggests that the user should touch the robot’s head to stop the session only in the case of an interaction loop or if the user is willing to stop the interaction.

All interactions will be recorded on video using a GoPro camera placed behind the robot. The robot will be placed in a dedicated area, and only one user will be permitted at a time to ensure that no data is collected about “unaware individuals.” These videos will be used for postanalysis to assess the emotional aspect of the interaction using the FaceReader system of Noldus in the “Youse” Usability Lab, which is located within the library of the Institute.

#### Postinteraction Assessment

A brief interview will be administered after the interaction to assess satisfaction with the service. The SUS scale will be used to measure usability grade and the HRI scale will be used to assess HRI.

### Statistical Analysis

Sample size determination followed feasibility study conventions rather than power calculations for confirmatory testing. Previous studies evaluating patient satisfaction with novel health care service innovations enrolled 124 to 177 participants [26,27]. To provide robust descriptive data across both feasibility indicators (recruitment, completion, and acceptability) and the balanced quasi-experimental design (n=100 per robot), the HOSPER study targets 200 participants (100 Nao and 100 Pepper). This sample size supports reliable estimation of prevalence estimates (eg, satisfaction proportions) while remaining practical for a single-center pilot. In the case that the statistical analysis reveals a positive trend, a new protocol will be proposed with the aim of conducting a trial.

Continuous variables will be reported as mean and SD, or median and IQR, depending on their distribution (as assessed using the Kolmogorov-Smirnov). Categorical variables will be expressed as absolute numbers and percentages.

Descriptive statistical analysis will be conducted on quantitative data with SPSS (Statistical Package for the Social Sciences; IBM Corp) and RStudio (Posit PBC). The robot’s logs (computer records) will be extracted in order to make a technical assessment of the objective parameters of HRI: dialogue comprehension ability, questions asked, answers given, dialogue duration, and so on.

Moreover, HRI will be analyzed using the Noldus system, considered the gold standard for behavioral analysis. Specifically, FaceReader and Observer (Noldus Information Technology) will be used to analyze audio-video recording of interactions. FaceReader uses facial analysis to identify the Ekman 7 emotions (neutrality, happiness, anger, sadness, disgust, fear, and surprise) in real-time [28] and summarize emotional valence distributions. Instead, the Observer enables the analysis of the interaction quantitatively and qualitatively by manually inserting labels to code the user’s emotional state and behaviors. Results will describe emotional and behavioral patterns during robot interactions to complement self-reported questionnaires. These analyses can be integrated and stacked with the Noldus software, enabling correlations to be found between the robot’s actions and the user’s behavior. This observational approach is useful for describing the dynamics of interaction and assessing the user’s experience.

Finally, the comparison between groups (Nao vs Pepper) will be carried out with a 2-tailed *t* test or the Mann-Whitney *U* test and the Fisher exact test considering the variables typology and distribution. As this is a feasibility study, these comparisons are descriptive only and not powered for formal inference. Linear or logistic regression models may be used exploratorily to examine potential confounders, but results will not support causal conclusions.

Due to the enrollment of the older population, despite the short duration of the testing and the presence of a researcher, it could happen to have missing data. Missing data will be reported by variable and time point. Moreover, available case analysis will be used for descriptive summaries, with complete-case denominators for primary outcome and feasibility indicators.

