**Figure 1. F1:**
[figure not shown]
The study design. SPMSQ: Short Portable Mental Status Questionnaire; SUS: system usability scale.

A total of 200 older adults will be recruited for this single-center feasibility pilot with a pragmatic quasi-experimental design. For logistical reasons, entire days will be dedicated to either Nao or Pepper. Participants will be equally allocated to interact with Nao or Pepper based on alternating study days and a predetermined quota system: once 100 participants have interacted with one robot, all subsequent participants will use the other robot until a total of 100 participants are reached for each. The allocation schedule will be predetermined and documented to ensure transparency.

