### Procedure

#### Recruitment (T0)

The robots will be placed in a dedicated area (a closed box) at the hospital entrance. Only one user will be allowed in at a time. A researcher will stop users at the hospital entrance and invite them to participate in the study. Participants must confirm their willingness to participate in writing. After signing the consent forms, the technology will be assigned to them in a randomized alternating manner (ABAB) according to the order of inclusion of participants. Then, the researcher will collect general information about the patient and administer the cognitive scale to verify that the user meets the inclusion criteria.

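### If robots are allocated by whole study days, the planned Nao-Pepper tests ignore the day and their p-values will be too small; the conflicting allocation rules must be reconciled first

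*Protocol article*

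**What the plan says.** The protocol article gives two allocation rules.

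- Study Design (text under Figure 1): "entire days will be dedicated to either Nao or Pepper". It adds: "Participants will be equally allocated to interact with Nao or Pepper based on alternating study days and a predetermined quota system". A quota follows: "once 100 participants have interacted with one robot, all subsequent participants will use the other robot".
- Recruitment (T0): after consent, "the technology will be assigned to them in a randomized alternating manner (ABAB) according to the order of inclusion of participants". This is allocation person by person, so both robots would be in use on the same day.

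On size, Statistical Analysis says that "the HOSPER study targets 200 participants (100 Nao and 100 Pepper"), and that "Sample size determination followed feasibility study conventions rather than power calculations for confirmatory testing".

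On the comparison, the same section says that "the comparison between groups (Nao vs Pepper) will be carried out with a 2-tailed" t test, a Mann-Whitney U test or a Fisher exact test, depending on the type and distribution of the variable. No term for study day is named. Regression is optional and aimed at confounders. The section qualifies all this: "these comparisons are descriptive only and not powered for formal inference". It states no alpha, no decision rule and no confidence interval for this comparison.

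**The concern.** Under the Study Design rule the day, not the participant, is the unit allocated. All three tests assume independent participants. People seen on the same day may share the attending researcher, who may be a psychologist or a physician, and any malfunction or interruption, which the protocol expects and plans to note. Because each day belongs to one robot, such shared influences go wholly into the Nao-Pepper contrast. A standard error computed as if there were 100 independent people per robot is then too small, and so is the p-value.

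What is at stake is limited: a chance difference between the robots, for example on the usability scale, could be read as better supported than it is. In addition, if a later trial also allocates by day, it will need the day ICC, and the stated analysis would not produce one.

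**Working it through.** **The plan's own figure.** The total is 100 + 100 = 200. There is no power calculation to reproduce, since no alpha, power, effect size or SD is given.

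**Inputs.** From the article: 100 per robot; whole-day allocation (Study Design) or ABAB by participant (Recruitment); two-tailed tests without a day term (Statistical Analysis). Assumed, because the article does not state them: nominal alpha 5%, participants per day *m* from 1 to 20, and ICC from 0.01 to 0.10.

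**Formulas for whole-day allocation.** Design effect DE = 1 + (*m* − 1) × ICC. The naive standard error is too small by a factor √DE. Effective number per robot = 100/DE. True two-sided error of the naive test = 2 × [1 − Φ(1.96/√DE)].

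Example, *m* = 10 and ICC = 0.05: DE = 1 + 9 × 0.05 = 1.45; √1.45 = 1.204; 100/1.45 = 69.0; 1.96/1.204 = 1.628; true error 10.4%.

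The last two columns are t-test rejection rates from 10,000 simulated null trials of 200 people.

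| *m* | ICC | DE | √DE | Effective n per robot | True error, formula | Simulated, whole days | Simulated, ABAB |
|---|---|---|---|---|---|---|---|
| 1 | any | 1.00 | 1.000 | 100 | 5.0% | not run | not run |
| 2 | 0.01 | 1.01 | 1.005 | 99.0 | 5.1% | 4.8% | 4.8% |
| 2 | 0.10 | 1.10 | 1.049 | 90.9 | 6.2% | 6.4% | 4.1% |
| 5 | 0.05 | 1.20 | 1.095 | 83.3 | 7.4% | 7.4% | 4.5% |
| 10 | 0.05 | 1.45 | 1.204 | 69.0 | 10.4% | 10.8% | 4.4% |
| 10 | 0.10 | 1.90 | 1.378 | 52.6 | 15.5% | 15.8% | 4.0% |
| 20 | 0.10 | 2.90 | 1.703 | 34.5 | 25.0% | 25.4% | 3.9% |

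Mann-Whitney results were nearly the same. Under ABAB, across both tests and every scenario simulated, the error rate lay between 3.6% and 5.1%. The Fisher test was not simulated.

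**Does ignoring the day distort the quantities carried to a later trial?** With equal day sizes, the expected sample variance within a robot group, relative to the true variance, is (n − DE)/(n − 1). For n = 100 and DE = 1.90 this is 98.1/99 = 0.991, so a sample size based on that SD would be about 1% too small. The mean difference itself is not biased by ignoring clustering.

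**The case against.** The strongest reply is that the article already limits this comparison. It calls it descriptive, rules out causal conclusions from the regression models, sets no alpha, and bases neither the primary end point nor any of the three feasibility criteria on it. That stands, and it caps the importance. It does not remove the point: the caveats concern power and causality, whereas the problem is that the stated tests do not fit the stated allocation. Nor is this a detail left to an unseen analysis plan, because the tests are named here.

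Second, whole-day allocation is not settled. Under the Recruitment (T0) rule the optimism disappears. That also stands, so the point is conditional.

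Third, the size rests on assumptions. Recruiting 200 people over 12 months is about 17 a month. At one or two a day the true error is only 5.0% to 6.2%; at ten a day all recruitment would fit into 200/10 = 20 days. The article does not give the number of study days, so the low end is as open as the high end. The closed area and identical scripts may also keep the ICC small.

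Some stronger readings are tempting but unsupported:

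- A reader might infer that planned confidence intervals are too narrow. None is planned for this comparison.
- A reader might infer that the tests will choose a robot. No section says so. The condition about a positive trend in Statistical Analysis is not tied to the Nao-Pepper contrast.
- A reader might infer that the SD and difference carried forward will understate a later trial's size. As shown above, the effect on size is about 1%; the relevant gap is the missing day ICC, and only if that trial allocates by day.

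**Conclusion.** The point holds conditionally. If the Study Design rule is what runs, the planned t, Mann-Whitney and Fisher tests ignore the unit of allocation, and their p-values are too small whenever several people are seen per day and outcomes correlate within the day. Under the assumed values the true error of a nominal 5% test ranges from 5.0% to about 25%, with 7.4% and 10.4% as middle cases (five and ten per day, ICC 0.05). The article does not allow the figure to be narrowed. If the Recruitment (T0) rule runs, the tests are level or slightly conservative. The contradiction between the two rules therefore comes first. Importance is minor to moderate, since no stated trial conclusion depends on this comparison.

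**What to change.** 1. Reconcile Study Design with Recruitment (T0), so that one allocation rule is stated.
2. If days are the unit, record the study day for every participant. Data Management offers a dated video file name only as one of two examples, so this should be made explicit.
3. Replace the independent-samples tests with the Nao-Pepper difference and its 95% confidence interval, from a model with robot as a fixed effect and study day as a random intercept, or with day-clustered standard errors and a small-sample correction. The correction matters if days are few: at twenty per day there would be only 200/20 = 10 days, five per robot.
4. Report the day ICC for the later trial.

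The cost is a few lines of code in software the article already names, with no extra participants or procedures. The downside is somewhat wider stated uncertainty. The change does not deal with the quota switch: once one robot reaches 100, the remaining days may all belong to the other, which mixes robot with calendar time. A term for day does not remove that.

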### Outcomes

#### Overview

The primary end point of the study is the assessment of the perceived quality of an innovative reception service, as measured by the Customer Satisfaction Questionnaire.

The secondary end points are (1) assessment of the usability of 2 robotic platforms by older adults for hospital reception, as measured by the system usability scale (SUS) [22]; (2) analysis of HRI using the Godspeed Questionnaire [23]; (3) dynamic analysis of the interaction and user experience using the Noldus system [24]; and (4) analysis of robot logs to assess technical performance.

As this is a feasibility study, these outcomes will be interpreted descriptively. For the primary end point, we will examine mean scores on the Customer Satisfaction Questionnaire and the proportion of participants reporting medium-to-high satisfaction levels to judge whether the robot-mediated reception service is acceptable to older adults. For the secondary end points, the distributions of SUS, Godspeed Questionnaire scores, and Noldus-derived emotional indicators will be used to evaluate whether usability, HRI quality, and emotional responses are compatible with moving towards a larger-scale trial. In addition to these measures, the study will use standard feasibility indicators, including recruitment rate, the proportion of participants who complete the interaction and postinteraction assessments, and completeness of data collected at T0 and T1. These indicators will be summarized descriptively to judge whether the protocol is feasible in routine practice. Finally, qualitative notes on technical performance (eg, malfunctions, interruptions, or need for operator intervention) will be collected throughout the study both during the sessions and through the analysis of video recordings to inform the system-level feasibility of the robot-mediated reception service and guide future updates of the service.

While outcomes focused on usability and HRI emphasize validated patient-reported measures, triangulation is provided through existing data sources: Noldus video analysis for objective emotional and behavioral indicators, and robot logs capturing interaction duration, comprehension rates, and repetition requests as objective efficiency metrics. In fact, these complementary data sources mitigate self-report limitations while remaining within the approved protocol scope.

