Finally, as this is a feasibility pilot, a priori success criteria are defined. The study will be considered feasible if: (1) at least 70% of eligible older adults approached agree to participate; (2) at least 70% of enrolled participants complete the interaction with the assigned robot and the postinteraction assessment; and (3) questionnaire data are complete for at least 80% of enrolled participants. These thresholds are intended to inform the design and sample size of a subsequent definitive trial rather than to support hypothesis testing.

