### Risks and Benefits Analysis

This study involves risks and benefits for participants. Expected benefits include the possibility that participants may feel more supported during reception, thanks to standardized information and dedicated guidance from the robots. Risks are minimal, but not absent. There is a risk that older people will stop interacting with the robots (eg, because they dislike Pepper and Nao or because they are afraid to interact with 2 humanoid robots). If this were to happen, the session would be interrupted and concluded immediately.

As the presence of the 2 robots could cause distress, participants will interact with them in an environment that guarantees an adequate level of privacy during the interaction.

To protect the security of participants, the following measures have been adopted:

Placement of robots within a dedicated structure that allows private data collection without external interference and ensures a human-robot interaction that respects user privacy and security;The robots will function in plug-in mode to avoid service interruption and to limit their free movements. They will remain static, although they are free to gesticulate and move their heads, as these are essential aspects of empathetic interaction;Clear and complete information about the appropriate use of the robots (eg, they must not lean on the devices or make any movements that could destabilize them);The researcher will be present in the study area throughout the interactive session to adequately train participants on the use of robots and provide assistance in case of difficulties or problems, without impacting interaction;All phases will also be illustrated with easily interpretable iconographic material to guide the researcher.

Despite the precautions described above, adverse events may still occur: (1) participants will be asked not to touch or disconnect the robot in case of problems or malfunctions; (2) participants should call the researcher if they experience any difficulties; and (3) when called by participants, the researcher will ensure that no damage has been caused to anyone or to the robots.

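### The missing-data rule puts the feasibility indicators on complete cases, while the completion and completeness criteria are defined on all enrolled participants; both cannot be followed

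*Protocol article*

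**What the plan says.** Three statements in the protocol article bear on this point.

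- **Success criteria (Outcomes, Overview).** The pilot counts as feasible if three conditions hold. The second is that "at least 70% of enrolled participants complete the interaction with the assigned robot and the postinteraction assessment". The third is that "questionnaire data are complete for at least 80% of enrolled participants". Both name enrolled participants as the denominator. The first condition has a different base: "at least 70% of eligible older adults approached agree to participate".
- **What the feasibility indicators are (Outcomes, Overview).** Besides the recruitment rate, they are "the proportion of participants who complete the interaction and postinteraction assessments, and completeness of data collected at T0 and T1". These are the quantities that criteria 2 and 3 judge.
- **Missing-data rule (Statistical Analysis, last paragraph).** The rule is that "available case analysis will be used for descriptive summaries, with complete-case denominators for primary outcome and feasibility indicators". The sentence just before it promises that missing data will be reported for each variable and time point.

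The planned enrolment is 200, with 100 per robot.

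**The concern.** A completion rate exists to count the people who did not complete, and a completeness rate to count the people with gaps in their data. A denominator restricted to complete cases removes exactly those people. An analyst who follows the Statistical Analysis section therefore cannot obtain the rates that the success criteria define, and one who follows the criteria breaks the missing-data rule.

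The pilot's headline conclusion is at stake. The abstract names completion rates as a specific focus, the Discussion expects adequate rates against the predefined thresholds, and the thresholds are meant to inform the design and sample size of a later trial. The protocol also foresees the losses concerned. The Risks and Benefits Analysis anticipates participants who stop because they dislike or fear the robots, and the Statistical Analysis section anticipates missing data in this age group. While both rules stand, the denominator could be chosen after the data are seen.

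**Working it through.** The plan has no calculated figure to reproduce here: the sample size follows convention and the thresholds are set in advance. The check is direct arithmetic on the two denominators.

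**Inputs**
- Planned enrolment N = 200 (Statistical Analysis).
- Criterion 2: at least 70% of enrolled; criterion 3: at least 80% of enrolled (Outcomes, Overview).
- Missing-data rule: complete-case denominator (Statistical Analysis).
- c = number of complete participants, which is hypothetical because the documents give no expected value.

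**Step 1. Thresholds as counts on the enrolled denominator**
- Criterion 2: 0.70 × 200 = 140 participants.
- Criterion 3: 0.80 × 200 = 160 participants.

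**Step 2. The two rates**
- Enrolled denominator: c / 200.
- Complete-case denominator: c / c = 100% for every c > 0.

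In this table a complete case has finished the interaction and the assessment and has full questionnaires, so the same c serves both criteria.

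| c | c/200 | Criterion 2 (≥70%) | Criterion 3 (≥80%) | c/c |
|---|---|---|---|---|
| 160 | 80.0% | met | met | 100% |
| 159 | 79.5% | met | not met | 100% |
| 140 | 70.0% | met | not met | 100% |
| 139 | 69.5% | not met | not met | 100% |
| 110 | 55.0% | not met | not met | 100% |

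With 160 or more complete, both denominators give the same verdict. From 140 to 159 the verdict on criterion 3 changes. Below 140 the verdicts on both criteria change.

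**Step 3. A narrower meaning of complete case for criterion 2**

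Suppose a complete case needs full questionnaires only. Someone may then stop the interaction early and still answer. Let s be the number of such people among the c complete cases. Criterion 2 is (c − s)/200 on enrolled and (c − s)/c on complete cases.

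- c = 120, s = 5: 115/200 = 57.5% against 115/120 = 95.8%.
- c = 120, s = 20: 100/200 = 50.0% against 100/120 = 83.3%.

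On this meaning criterion 2 is no longer fixed at 100%, but in both examples it fails on enrolled participants and passes on complete cases. Criterion 3 remains c/c = 100%.

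**The case against.** The best defence is that a specific definition governs a general rule. The success criteria state their own denominators, and the missing-data sentence is generic and does not claim to amend them. On a charitable reading, complete-case means that a participant's status on the indicator is known. Completion status would be known for essentially everyone enrolled, so the enrolled denominator would return. Also, the sample size paragraph uses the feasibility label for recruitment, completion and acceptability, and a complete-case base is ordinary for a questionnaire measure of acceptability.

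This does not remove the conflict. The text does not give the charitable meaning, the Outcomes overview expressly lists completion and data completeness as feasibility indicators, and nothing exempts criteria 2 and 3 from the rule.

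Two stronger inferences are tempting, and the objection is right to resist them.

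- A reader might infer that two of the three criteria can never fail. That is established only for criterion 3. Criterion 2 is exactly 100% only if a complete case must have finished both the interaction and the assessment. The Risks and Benefits Analysis says of a participant who stops, "If this were to happen, the session would be interrupted and concluded immediately", which leans towards that meaning, but it does not say whether the questionnaires are cancelled too.
- A reader might infer that the report would carry no information on drop-out or missing data. The promise to report missing data by variable and time point contradicts that. With those counts and the number enrolled, a reader could see the losses.

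It also stands that the thresholds serve planning and not hypothesis testing, and that the choice of denominator is harmless when completion is good.

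**Conclusion.** The point holds as a contradiction between two stated rules, and the missing-data sentence is wrong as written for these indicators. Taken literally, it fixes criterion 3 at 100% and inflates criterion 2 by an amount that depends on how a complete case is defined. The feasibility verdict changes only when the enrolled rate is below threshold: fewer than 160 of 200 for criterion 3, fewer than 140 of 200 for criterion 2. That is the situation the criteria exist to detect.

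This rests on the planned enrolment of 200 and on a literal reading of the rule; the completer counts are illustrations, not forecasts. Losses would remain visible in the missing-data report, but the criteria would be judged on the wrong base. Criterion 1 does not become 100% by construction. Using complete cases for the satisfaction outcome is a separate matter and no part of this contradiction.

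**What to change.** Delete the reference to feasibility indicators from the complete-case sentence in the Statistical Analysis section, so that the rule covers only the satisfaction outcome. Add that criteria 2 and 3 keep all enrolled participants as the denominator, and that anyone who stopped or has missing forms counts as not complete.

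A Wilson 95% interval beside each rate would be a useful option but is not needed to remove the conflict; at the thresholds it runs from about 63% to 76% for 140/200 and from about 74% to 85% for 160/200.

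The change is a matter of wording and needs no new data. The downside is that the reported percentages may be less favourable.

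### Satisfaction is summarised on complete cases, and the plan does not say whether people who stop early are still asked; if they are not, acceptability is overstated

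*Protocol article*

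**What the plan says.** Under Statistical Analysis, the article sets available-case summaries in general, "with complete-case denominators for primary outcome and feasibility indicators". The same paragraph promises that "Missing data will be reported by variable and time point", and it attributes missing data broadly to the age of the population.

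Under Risks and Benefits Analysis, it anticipates that some people will stop interacting, for example "because they dislike Pepper and Nao or because they are afraid to interact with 2 humanoid robots". It continues: "If this were to happen, the session would be interrupted and concluded immediately".

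Under Postinteraction Assessment and in Table 1, satisfaction is measured after the interaction. Neither place says what happens to the questionnaire when the interaction was cut short.

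Under Outcomes, Overview, the primary summaries are the mean score and "the proportion of participants reporting medium-to-high satisfaction levels to judge whether the robot-mediated reception service is acceptable to older adults". The same section sets three joint feasibility criteria: at least 70% of eligible people approached agree, at least 70% of enrolled participants complete the interaction and the assessment afterwards, and questionnaire data are complete for at least 80% of enrolled participants.

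**The concern.** The protocol names a reason for stopping that is itself a form of dissatisfaction, and then computes satisfaction only among people who have a questionnaire. If those who stop from dislike or fear are not asked, they leave both numerator and denominator, and the summary describes the people who were content to stay. The paragraph on missing data does not connect the two: it cites older age and does not mention the reasons for stopping given under Risks and Benefits Analysis.

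At stake is the acceptability judgement, which rests on this mean and proportion. The Statistical Analysis section also makes a follow-on trial protocol depend on a positive trend and presents the sample size as supporting reliable estimation of satisfaction proportions. If stoppers go unasked, more participants would not remove the error.

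**Working it through.** **The plan's own figure.** The only stated number is the target of 200, made up of 100 for Nao and 100 for Pepper. The sum agrees. No power calculation lies behind it, so there is nothing further to reproduce.

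**Inputs from the article**
- Enrolled: N = 200.
- Denominator for the primary outcome: complete cases.
- Smallest share with complete questionnaires that meets the third criterion: 80%, so at most 40 of 200 missing.
- Satisfaction items run from 1 to 7.

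**Assumptions.** The article gives no expected satisfied share among responders (p) or among the missing (q). Both are varied below.

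**Formula.** With c the share of enrolled participants who have a questionnaire:
- all-enrolled proportion = c·p + (1−c)·q
- complete-case proportion = p
- overstatement = p − [c·p + (1−c)·q] = (1−c)(p−q)

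**At the 80% completeness limit, p = 90%, q = 0**
- Complete cases: 144/160 = 90%, Wilson 95% CI 84–94%.
- All enrolled: 144/200 = 72%, Wilson 95% CI 65–78%.
- Gap: 0.20 × 0.90 = 18 points.

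**Gap in percentage points for p = 90%**

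| c | q = 0 | q = 20% | q = 50% | q = 90% |
|---|---|---|---|---|
| 95% | 4.5 | 3.5 | 2.0 | 0 |
| 90% | 9 | 7 | 4 | 0 |
| 80% | 18 | 14 | 8 | 0 |

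With q = 0 and c = 80%, the gap is 0.20 × 0.70 = 14 points if p = 70%, and 0.20 × 0.80 = 16 points if p = 80%.

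**Comparison with sampling error.** With 160 responders and p = 90%, the 95% half-width is 1.96 × √(0.9 × 0.1/160) = 4.6 points. At c = 80% the bias exceeds this when 0.20 × (0.90 − q) > 0.046, that is, when q is below about 67%.

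**The mean score behaves the same way.** If responders average 5.5 and the missing would have averaged 2 (both assumed), the mean is overstated by (1−c) × 3.5: 0.70 at c = 80%, 0.35 at 90% and 0.18 at 95%.

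**The case against.** **Stoppers may well be interviewed.** The article does not say that people who stop leave or go without the questionnaire. Under Interaction With the Robot (T1), the word session means the contact with the robot, which a touch on its head brings to an end. Stopping at any time is treated there as an ordinary way for the interaction to end, and Postinteraction Assessment sets no condition that the interaction was completed. The 80% questionnaire threshold beside the 70% completion threshold also fits some non-completers still giving data, though it does not prove it. This stands. A reader might infer that satisfaction is overstated by design, but the text leaves the matter open. If all stoppers are asked and answer, this bias does not arise.

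**The 70% threshold does not set the size.** A reader might put 140 of 200 into the formula and get 126/140 = 90% against 126/200 = 63%. With only 140 questionnaires, however, the 80% completeness criterion already fails. Nor is the all-enrolled figure always the complete-case figure times the completion rate; that requires every missing person to be unsatisfied. Some will stop for other reasons, such as an interaction loop.

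**The loss is partly visible.** Completion and data completeness are separate indicators, missing data are reported, interactions are filmed, the outcomes are read descriptively, and satisfaction has no pass mark among the feasibility criteria. This limits the consequence, but none of it corrects the satisfaction estimate. The safeguard is also weakened because the same sentence applies complete-case denominators to the feasibility indicators, whereas Outcomes, Overview defines completion and completeness over enrolled participants. With 120 completers of 200, those readings give 60% and 120/120 = 100%.

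**An unseen analysis plan may hold sensitivity analyses.** That is possible, and their absence here is not counted. The complete-case rule itself is stated in this document.

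**Conclusion.** The point holds conditionally. The complete-case rule for the primary outcome is explicit, a dissatisfaction-related reason for stopping is explicit, and what happens to the questionnaire after an early stop is not stated. To the extent that such stoppers are not asked, the error runs upward, towards finding the service acceptable.

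Its size cannot be fixed from the article. Within the protocol's own criteria it could reach 18 points under p = 90% and q = 0, well beyond sampling error. If 95% of participants answer, the same assumptions give 4.5 points; if the missing are as satisfied as the rest, it is zero. Because satisfaction is descriptive and has no threshold, no formal go decision changes, but the evidence on acceptability could mislead the design of the next trial.

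**What to change.** 1. State under Postinteraction Assessment that the satisfaction questionnaire is offered to every participant who starts the interaction, including those who stop early and are willing to answer. Record the reason for stopping.
2. Keep the complete-case mean and proportion. Beside them, report the satisfied proportion over all enrolled eligible participants who were assigned a robot, counting those without a questionnaire as not satisfied and labelling the result a lower bound. The word eligible is needed because the Recruitment (T0) text assigns the robot before the cognitive screen.
3. Show both figures by robot with the reasons for stopping, since losses may differ between Nao and Pepper.
4. Base the acceptability judgement on both figures.
5. While editing the missing-data sentence, reconcile its denominators for the feasibility indicators with those in Outcomes, Overview.

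The cost is wording, one more tabulated proportion and an existing questionnaire offered to a few more people. Recruitment was planned for January to December 2025, so step 1 can help only participants not yet seen; the bound needs only enrolment, assignment and questionnaire status. Its drawback is that it is conservative for people who left for reasons unrelated to the robot. It also merges satisfaction with completion, which is why it should accompany the complete-case figure and not replace it.
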